### Control population

The control population consists of the prospectively collected shock, tachycardia and event data combined from two randomized clinical ICD trials; the MIRACLE ICD Trial[13] and the EMPIRIC Trial. [11] Both of these trials included both primary and secondary prevention patients, but only the primary prevention patients were included in the control population for the PREPARE analysis.

Originally, the control population included only the primary prevention patient data from the MIRACLE ICD Trial. The MIRACLE ICD Trial was a multi-center randomized trial of 978 CRT-ICD patients, designed to assess the safety and effectiveness of biventricular CRT in primary and secondary prevention patients. However, in contrast to the MIRACLE ICD Trial which enrolled only patients receiving a cardiac resynchronization defibrillator (CRT+ICD), the PREPARE Study includes primary prevention patients implanted with either an ICD or CRT+ICD device. After an interim review of baseline characteristics during the enrollment phase of the PREPARE Trial, it became evident that 65% of the patient population did not require a cardiac resynchronization device. Therefore, the PREPARE Trial population was comprised of patients with more favorable clinical characteristics than the advanced heart failure patients enrolled in the MIRACLE ICD Trial. This imbalance threatened to falsely skew the results of the study, making it difficult to discern whether the potential efficacy of the PREPARE parameters would be the result of the recruitment of patients into the PREPARE study with less severe disease.

To address the imbalanced baseline characteristics between the PREPARE patients and the original control population, the primary prevention patients from the physician-tailored arm of the EMPIRIC study were combined with MIRACLE ICD control patients to produce the control population.

The EMPIRIC study was a multi-center randomized trial of 900 ICD patients, designed to compare standardized vs. physician-tailored VT/VF programming in both primary and secondary prevention patients. [11] The study was recently completed, and its patient population is thought to better reflect the higher ratio of ICD implant indications seen during enrollment into the PREPARE study than the MIRACLE ICD Trial, reported in 2003. [13] Additionally, there were a large number of patients (276) randomized in the EMPIRIC Trial to the physician-tailored arm who met the PREPARE Trial definition of primary prevention. These patients, along with the 415 primary prevention patients from the MIRACLE ICD Trial, have been combined, producing a total of 691 patients in the historical control sample.

When compared with PREPARE patient baseline demographics, the patient characteristics of the combined physician-tailored arm are not clinically different. The baseline clinical data for the study and control patients is listed in Table 1. This table includes baseline demographics which were collected in PREPARE, MIRACLE ICD and EMPIRIC. Demographics for MIRACLE ICD and EMPIRIC are shown separately and in combination.

**Table 1 T1:** Patient Demographics

	**PREPARE Patients** ** (N = 700)**	**MIRACLE ICD Patients** **(N = 415)**	**EMPIRIC Patients** **(N = 276)**	**Combined Control (MIRACLE ICD and EMPIRIC) Patients** **(N = 691)**

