### Statistical analysis

The primary endpoint is the difference in Morbidity Index incidence density between the study patients programmed to the PREPARE settings and the control population programmed to physician-tailored programming. The PREPARE programming strategy will be considered superior to the physician-tailored programming approach if a statistically significant reduction in the incidence density is demonstrated in the PREPARE group when compared to the historical control.

There were 347 shocked spontaneous VT/VF episodes, 4 events of arrhythmogenic syncope, and no episodes of untreated symptomatic sustained VT/VF in the 691 control population patients followed for 503 years (ID = 0.70). Assuming that the PREPARE programming strategy results in a 25% reduction in the number of shocked spontaneous VT/VF episodes, the rates of arrhythmogenic syncope and untreated symptomatic sustained VT/VF events remain the same, and the same number of years of follow-up, a total of 700 patients will provide at least 95% power for the primary hypothesis, tested at the two-sided significance level of 0.05. Both the Morbidity Index ID and the secondary analysis of the Morbidity Tachycardia Index ID will be tested using the comparison of incidence rates test. [22]

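### Superiority over historical controls rests on a crude rate comparison, although the article's own figures show material baseline and device-type imbalance between the groups it calls comparable

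*Protocol article*

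**What the plan says.** The Control population section explains that the control group was first drawn from MIRACLE ICD alone, a trial of CRT+ICD recipients only. An interim review of PREPARE baseline data changed that: "it became evident that 65% of the patient population did not require a cardiac resynchronization device". The authors saw that a healthier PREPARE population could be mistaken for a programming effect. Their response was to add the primary prevention patients from the physician-tailored arm of EMPIRIC (276) to those from MIRACLE ICD (415), making 691 controls. The section then concludes that "the patient characteristics of the combined physician-tailored arm are not clinically different" and refers to Table 1.

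The Statistical analysis section declares PREPARE programming superior "if a statistically significant reduction in the incidence density is demonstrated in the PREPARE group when compared to the historical control". The primary and key secondary indices "will be tested using the comparison of incidence rates test", with the primary hypothesis "tested at the two-sided significance level of 0.05". No covariate, stratum, matching or weighting is named. The Data collection section names two particular sources of bias against historical data, adverse event collection and episode adjudication. Case mix is not one of them.

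**The concern.** Without randomisation, a crude rate difference combines the effect of programming with any difference in the patients' underlying event rates. The authors identified this threat themselves. The remedy described is a wider control pool, after which the groups are treated as alike and the decision rests on a test that takes no covariates. If the pooled groups still differ on characteristics related to shocks or arrhythmia, the test can reach significance, or miss a real effect, for reasons unrelated to programming. The superiority claim would then be hard to interpret whichever way the result fell.

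**Working it through.** **1. The plan's own figures.** The Statistical analysis section gives the control data: "There were 347 shocked spontaneous VT/VF episodes, 4 events of arrhythmogenic syncope, and no episodes of untreated symptomatic sustained VT/VF" in "691 control population patients followed for 503 years (ID = 0.70").
- Control events: 347 + 4 + 0 = 351. Incidence density: 351/503 = 0.698, which matches 0.70.
- Expected PREPARE events under the design effect, with the same 503 years: 0.75 × 347 + 4 = 264.25.
- z = (351 − 264.25)/√(351 + 264.25) = 86.75/24.80 = 3.50. Power = Φ(3.50 − 1.96) = 93.8%, close to the stated 95%.

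This is therefore a fair representation of the planned test. With equal follow-up it reaches significance at about 300 PREPARE events: (351 − 300)/√651 = 2.00, a rate ratio of 300/351 = 0.855.

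**2. Imbalance, PREPARE v combined control.** Inputs are from Table 1, except for device type. The standardised difference is (m₁ − m₂)/√((s₁² + s₂²)/2) for means and (p₁ − p₂)/√((p₁(1 − p₁) + p₂(1 − p₂))/2) for proportions.

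| Characteristic | PREPARE | Control | Std. difference |
|---|---|---|---|
| LVEF, mean ± SD | 27.7 ± 10.5 | 24.7 ± 9.8 | 0.30 |
| Ischemic cardiomyopathy | 69.7% | 57.0% | 0.27 |
| Age, mean ± SD | 67.4 ± 12.2 | 65.5 ± 11.7 | 0.16 |
| NYHA IV | 18/700 = 2.6% | 44/691 = 6.4% | −0.18 |
| CRT device | about 35% | at least 60% | about −0.52 |
| Prior infarction | 60.1% | 55.8% | 0.09 |
| Male | 79.3% | 77% | 0.06 |

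Table 1 has no device row. The 35% is 100 − 65 from the interim review. The 60% is 415/691 = 60.1%, because every MIRACLE ICD control had a CRT+ICD device; any CRT patients from EMPIRIC would raise it.

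**3. NYHA class I.** The raw gap is 117/700 = 16.7% v 36/691 = 5.2%. The Table 1 footnote says EMPIRIC recorded NYHA only where heart failure was documented, so the 99 controls without a class are those without documented heart failure. If all 99 were class I, controls would be (36 + 99)/691 = 19.5%, and the gap would reverse. Counting the 99 as not class III/IV, III/IV is 286/700 = 40.9% v 317/691 = 45.9% (−0.10).

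**4. What device mix alone could do.** Let k be the event rate of CRT patients relative to ICD-only patients. The article gives no such rate, so k is an assumption. With no programming effect, shares of follow-up equal to shares of patients, and controls at the 60.1% minimum:

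rate ratio R = (0.65 + 0.35k)/(0.399 + 0.601k); expected PREPARE events E = 351R; z = (351 − E)/√(351 + E).

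| k | R | E | z (positive favours PREPARE) |
|---|---|---|---|
| 0.5 | 1.18 | 413.8 | −2.27 |
| 0.67 | 1.10 | 387.7 | −1.35 |
| 1.2 | 0.96 | 335.3 | 0.60 |
| 1.5 | 0.90 | 317.2 | 1.31 |
| 2 | 0.84 | 296.0 | 2.16 |
| 2.5 | 0.80 | 281.6 | 2.76 |

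The chance of declaring PREPARE superior with no programming effect is Φ(z − 1.96): 26% at k = 1.5 and 58% at k = 2, against a nominal 2.5%.

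**The case against.** The authors did act on the imbalance. Controls were restricted to primary prevention patients, and adding EMPIRIC cut the LVEF standardised difference from 0.76 (27.7 ± 10.5 v 21 ± 6.8 in MIRACLE ICD alone) to 0.30. Median LVEF is 25 in both groups, median age is 68.7 v 67.7, and sex and prior infarction are close. This stands, but it describes a smaller imbalance, not its absence. Pooling also left device type, which prompted the change, at about 35% v at least 60%.

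The NYHA evidence is weaker than it first appears. The class I gap depends on how EMPIRIC collected the item, and a comparison restricted to classified patients drops the less sick controls. That objection stands in full; only the class IV difference is used here.

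The article is a condensed account, and a fuller plan may contain adjusted analyses. That is possible, so the absence of sensitivity analyses is not the point. The fault lies in what the article does fix: the comparability statement, and an unadjusted test as the deciding analysis.

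A reader might infer that adjustment was left out because the groups were judged similar. The article gives no reason, so this remains an inference.

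**Conclusion.** The point holds. The comparability statement conflicts with the article's own figures: LVEF, ischemic aetiology and device type differ by more than 0.25 standard deviations, and age and NYHA IV by 0.16 to 0.18. The test that decides superiority does nothing about this.

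A reader might go further and conclude that the comparison is biased in favour of PREPARE. The documents do not support that. PREPARE patients have higher LVEF, less class IV disease and fewer CRT devices, but they are older and more often ischemic, and no event rates by covariate are given. The net bias cannot be signed. Under the stated assumptions, device mix alone moves the rate ratio from 1.18 (k = 0.5) to 0.80 (k = 2.5). The expected z favours PREPARE significantly only at k of about 2 or more; at 1.5 it is 1.31, and at 0.5 it is significant against PREPARE. These figures rest on the interim 35% CRT share, the minimum 60% control share, equal follow-up of 503 years, and Poisson variation. Since the crude result could mislead in either direction, adjustment belongs in the primary analysis.

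**What to change.** - Make the primary analysis a rate model with a person-time offset, adjusted for device type (CRT v ICD-only), LVEF, ischemic aetiology, prior infarction, age and sex.
- Do not give NYHA a separate level for uncollected values. No PREPARE patient has that level, so a propensity model would separate perfectly on it, and the model would in effect discard the 99 controls without documented heart failure, drawn from the very source added to correct the imbalance. Use class III/IV v other, with those 99 in the other group, or confine NYHA to a sensitivity analysis.
- Report the effect within CRT and ICD-only strata, and against each control source separately. All ICD-only controls must come from EMPIRIC (at most 276), so the two sets of results should be read together.
- Keep the crude comparison as supportive.
- Replace the comparability sentence with the standardised differences, and add a device-type row to Table 1.

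The cost is a change of analysis wording and some loss of precision. The other covariates are already in Table 1. Device type is not reported for the EMPIRIC controls and must be retrieved. No further patients are needed.

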**Gender (N, %)**				
Male	555 (79.3%)	310 (74.7%)	222 (80.4%)	532 (77%)
Female	145 (20.7%)	105 (25.3%)	54 (19.6%)	159 (23%)

**Age (years)**				
Mean ± Standard Deviation	67.4 ± 12.2	65.4 ± 11.5	65.6 ± 12	65.5 ± 11.7
Median	68.7	67.9	67.3	67.7
Minimum – Maximum	19.2 – 92.2	31 – 89	23.3 – 91.4	23.3 – 91.4
n (%)	700 (100%)	415 (100%)	276 (100%)	691 (100%)

**Baseline Left Ventricular Ejection Fraction (%)**				
Mean ± Standard Deviation	27.7 ± 10.5	21 ± 6.8	30.3 ± 11	24.7 ± 9.8
Median	25	20	30	25
Minimum – Maximum	5 – 80	6 – 35	5 – 70	5 – 70
n (%)	691 (98.7%)	413 (99.5%)	273 (98.9%)	686 (99.3%)

**Baseline New York Heart Association Classification (N, %)**				
Class I	117 (16.7%)	0 (0%)	36 (13%)	36 (5.2%)
Class II	297 (42.4%)	137 (33%)	102 (37%)	239 (34.6%)
Class III	268 (38.3%)	237 (57.1%)	36 (13%)	273 (39.5%)
Class IV	18 (2.6%)	41 (9.9%)	3 (1.1%)	44 (6.4%)
Not Collected*	0 (0%)	0 (0%)	99 (35.9%)	99 (14.3%)

**Ischemic Cardiomyopathy**	488 (69.7%)	238 (57.5%)	155 (56.2%)	393 (57.0%)

**Myocardial Infarction (N, %)**	421 (60.1%)	193 (46.6%)	192 (69.6%)	385 (55.8%)

N/A = not collected

*NYHA Class was only collected in the EMPIRIC Trial for patients with documented heart failure

#### Programming

The strategies for reducing shock morbidity are to 1) reduce over-treatment of self-terminating tachycardias, 2) reduce the mis-identification of supraventricular arrhythmias as ventricular arrhythmias, and 3) terminate ventricular tachycardia with anti-tachycardia pacing as frequently as possible. Since the patients enrolled in this trial had never experienced a sustained ventricular arrhythmia, the parameters were chosen to not treat: 1) slow and presumably less symptomatic tachycardias, and 2) faster but self-terminating arrhythmias.

The exact tachycardia detection and therapy parameters for the PREPARE study are listed in Table 2. In summary two therapy zones are programmed, treating all rhythms of cycle length less than 330 ms that meet the duration criteria of 30 of 40 intervals. A single anti-tachycardia burst is provided for tachycardias between 330 and 240 ms. If the rhythm persists after ATP, a shock is provided. Rhythms faster than 240 ms receive shocks as the first therapy. A monitor zone is provided for tachycardia between 360 and 330 ms. Many SVT discriminators are programmed ON.

**Table 2 T2:** PREPARE Study VT/VF Programming

**ICD Parameter**	**Marquis/Maximo Family Programmed Value**
**INDUCTION**	

VF Detection	ON
VFDI	330 ms
VF NID	30/40
VF RNID	9/12

**DUAL CHAMBER**	

AF/AFl	ON
Sinus Tachcardia	ON
1:1 VT-ST Boundary	66%
Other 1:1 SVT	OFF
SVT Limit	300
Stability	OFF

**SINGLE CHAMBER**	

Wavelet	On, Match Threshold 70%
Stability	40
Onset	88%

**ALL**	

VF Detection	ON
VFDI	330 ms
VF NID	30/40
VF RNID	9/12
FVT	Via VF
FVTDI	240 ms
VT Detection	Monitor
VTDI	360 ms
VT NID	32
HR Timeout	OFF
VF Rx 1–6 Status	ON
VF Rx 1–6 Energy	30 or 35J maximum output of the ICD
VF Rx 1–4 Pathway	AX->B
VF Rx 5–6 Pathway	B->AX
VF Confirmation	YES
FVT Rx 1–6 Status	ON
FVT Rx 1 Type	Burst
FVT Rx 1 Initial # Pulses	8
FVT Rx 1 R-S1 Interval	88%
FVT Rx 1 # sequence	1
FVT Rx 1 Smart Mode	OFF
FVT Rx 2–6 Type	CV
FVT Rx 2–6 Energy	30 to 35J maximum output of ICD
FVT Rx 2–5 Pathway	AX->B
FVT Rx 6 Pathway	B->AX
VT Rx 1–6	OFF
Other Diagnostic and Therapy parameters	Nominals

The tachycardia detection and therapy parameters for the MIRACLE ICD and EMPIRIC patients included in the control arm were chosen at the discretion of the investigators and are referred to as "physician-tailored" parameters. [14]

#### Data collection

These data are collected at the 6 and 12 month scheduled visits and at unscheduled visits: cardiovascular adverse events, cardiovascular medications, VT/VF and SVT episodes, and patient diary.

Adverse events of syncope, near-syncope, and dizziness are collected between visits in a patient diary and evaluated for arrhythmogenic syncope, i.e. syncope or near syncope caused by a VT/VF or SVT episode, and symptomatic VT/VF events i.e. VT/VF events that result in the symptoms of near syncope or dizziness. All events in the PREPARE, EMPIRIC and MIRACLE ICD Trials will be adjudicated by the PREPARE Adverse Event Advisory Committee (AEAC) to identify arrhythmogenic syncope, near-syncope, and dizziness. The review includes the details surrounding each adverse event and the available EGM data for episodes occurring within 24 hours of the event. For the historical controls, where these adverse events were not as rigorously collected, the event will be adjudicated when the record indicated syncope, near-syncope, or dizziness in the narrative of an adverse event.

The differences in data collection methods between studies are always of concern when utilizing a historical control. There are two particular sources of bias when comparing the primary and key secondary endpoints in the PREPARE study to the historical control data: 1) adverse event collection and 2) incomplete adjudication of VT/VF episodes.

Patients in the PREPARE study are required to record adverse events of syncope, near-syncope, and dizziness in a patient diary, in an effort to increase the probability of collecting all occurrences of these events. By contrast, the MIRACLE ICD study relied on patient recall at study visits, and only system and procedure-related adverse events were collected in the EMPIRIC study. These methods of collection in the historical control group likely led to underreporting of syncope related events, and therefore decreased the probability of arrhythmogenic syncopal or symptomatic VT/VF event discovery during these studies. The expected consequence of this data limitation is that higher rates of arrhythmogenic syncope and symptomatic VT/VF events will be recorded in the PREPARE study.

Not all episodes in the MIRACLE ICD study were originally adjudicated for the spontaneous/induced and true VT/true SVT classifications. To avoid the bias that would be incurred by dropping these episodes with missing information, these will be reviewed and classified by an internal Medtronic VT/VF scientist prior to the completion of the PREPARE study.

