#### Morbidity index

The components of the Morbidity Index are:

• Syncope (secondary to tachyarrhythmia or presumed tachyarrhythmia)

• Untreated sustained symptomatic VT/VF events

• Episodes of spontaneous ventricular tachyarrhythmia that result in device-delivered shock

• Episodes that result in an inappropriate device-delivered shock.

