### Design

The PREPARE study is a prospective, single arm, multi-center cohort study designed to evaluate the efficacy of a pre-specified strategic profile of VT and VF detection and therapy settings designed for ICD indicated patients with no history of spontaneous sustained symptomatic VT or VF. All study patients received a Medtronic Marquis family ICD system with or without capacity for cardiac resynchronization implanted between October 2003 and April 2005. Approximately 700 patients were enrolled in the United States and the Netherlands and were programmed to the PREPARE parameters and followed for endpoints for 12 months after PREPARE programming.

For the purposes of this study, primary prevention patients are defined as those patients indicated for ICD or CRT + ICD implantation without a baseline history of ventricular fibrillation, ventricular flutter, monomorphic VT, polymorphic VT, or Torsades de Pointes. Patients may have a history of cardiovascular syncope, since the PREPARE findings are intended to be generalized to the primary prevention patient population seen in clinical practice.

• Inclusion criteria required:

○ Initial implantation for primary prevention ICD indications or

○ Prior ICD implantation within 6 months without subsequent

spontaneous VT/VF episodes

• Patients were excluded for:

○ History of spontaneous sustained symptomatic ventricular arrhythmias,

○ An electrophysiology test in the past, with sustained inducible VT < 180 bpm,

○ Any ICD implanted greater than 6 months prior to the study,

○ An ICD implanted within the previous 6 months, with subsequent history of a spontaneous episode of VT or VF appropriately treated with either ATP or shock.

○ Heart transplant

○ Mechanical right heart valve.

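### MIRACLE ICD episodes lacking adjudication are classified by the device maker's own scientist, with no stated masking to trial, leaving the control count open to bias of unknown direction and size

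*Protocol article*

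**What the plan says.** The Data collection section names two particular sources of bias against the historical control: "1) adverse event collection and 2) incomplete adjudication of VT/VF episodes". On the second, it reports that "Not all episodes in the MIRACLE ICD study were originally adjudicated for the spontaneous/induced and true VT/true SVT classifications". Rather than drop those episodes, "these will be reviewed and classified by an internal Medtronic VT/VF scientist prior to the completion of the PREPARE study".

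The study devices come from the same company. The Design section states: "All study patients received a Medtronic Marquis family ICD system with or without capacity for cardiac resynchronization".

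Events from all three trials also go to a committee, but for a different purpose. They are "adjudicated by the PREPARE Adverse Event Advisory Committee (AEAC) to identify arrhythmogenic syncope, near-syncope, and dizziness". That remit does not include the rhythm class of shocked episodes.

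The classification feeds the primary endpoint. One component in the Morbidity index section is "Episodes of spontaneous ventricular tachyarrhythmia that result in device-delivered shock", and inappropriate shocks are another. The Statistical analysis section gives the control count: "There were 347 shocked spontaneous VT/VF episodes, 4 events of arrhythmogenic syncope", with no untreated symptomatic sustained VT/VF, over 503 years.

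**The concern.** The trial has one arm, so the primary result depends as much on the historical control rate as on PREPARE's own events. Part of that control rate is still to be set by a judgement on each MIRACLE ICD episode that lacks a label. As described, every episode in the batch comes from a trial that serves only as a control, so its source is known unless something is done to hide it. The stated reader is employed by the manufacturer.

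A shocked episode labelled spontaneous counts as a control event. Labelled induced, it does not. Each net shift of 10 episodes moves the control incidence density by 10/503 = 0.02 per year. Even a neutral reader could not show neutrality under this arrangement. Setting the work before PREPARE is complete limits knowledge of the final result, but it neither hides the source trial nor places the review before PREPARE outcomes begin to accrue.

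**Working it through.** **Inputs**
- Control events (Statistical analysis): 347 + 4 + 0 = 351 in 503 years.
- Planned effect (Statistical analysis): 25% fewer shocked spontaneous VT/VF episodes, other rates unchanged, same follow-up. Expected PREPARE events: 0.75 × 347 + 4 = 264.25.
- Test (Statistical analysis): comparison of two incidence rates, two-sided 0.05, stated power at least 95%.
- MIRACLE ICD share of the control (Control population): 415/691 = 60% of patients.
- Number of unadjudicated episodes: not given.

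**The plan's own figures**
- Incidence density: 351/503 = 0.698, against the stated 0.70.
- Treating both counts as Poisson with equal follow-up: z = (351 − 264.25)/√(351 + 264.25) = 86.75/24.80 = 3.50.
- Power = Φ(3.50 − 1.96) = 93.8%. This is about one point below the stated figure and close enough to use as the base.

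**Weight of the classified component**
- Shocked episodes are 347/351 = 99% of the control count. The syncope component, which the committee does adjudicate, supplies 4.

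**Over-count of k control events, no true effect** (351 expected per arm)

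Expected z = k/√(702 + k). Chance of falsely declaring PREPARE superior = Φ(z − 1.96). With k = 0 this is 2.5%, the favourable half of the two-sided 0.05.

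| Net over-count | k | Expected z | False superiority |
|---|---|---|---|
| 2% | 7.0 | 0.26 | 4.5% |
| 5% | 17.6 | 0.65 | 9.6% |
| 10% | 35.1 | 1.29 | 25% |
| 15% | 52.6 | 1.92 | 48% |

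Setting k/√(702 + k) = 1.96 gives k ≈ 54, or 15% of 351.

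**Under-count of k control events, planned effect true**

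Power = Φ[(351 − k − 264.25)/√(351 − k + 264.25) − 1.96].
- 5% (k = 17.6): z = 69.2/√597.7 = 2.83, power 81%.
- 10% (k = 35.1): z = 51.65/√580.15 = 2.14, power 57%.

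**Which label moves the count**
- Spontaneous versus induced: induced takes a shocked ventricular episode out of the index.
- VT versus SVT: under the Morbidity index section, appropriate and inappropriate shocks both count, so relabelling a shocked spontaneous episode leaves the total unchanged. Under the narrower description in Statistical analysis and Summary, which counts shocked spontaneous VT/VF, the label can move it.

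**The case against.** - **The article may simply be silent on masking.** It condenses a full protocol, and masking or a second reader may be set out there or in an adjudication charter. This stands in part: unmasked reading is an inference from the composition of the batch, not something the article states. But the article does more than stay silent. It presents this procedure as its answer to a bias that it names, and the procedure is an in-house reader applied to one source trial.
- **A reader might infer that PREPARE episodes receive an independent review that the control episodes are denied.** The article does not say who classifies rhythm episodes in PREPARE or EMPIRIC. The same scientist may do so, and the committee is not assigned PREPARE rhythm episodes either.
- **A reader might infer that the bias favours PREPARE.** Nothing fixes its direction: an over-count helps PREPARE and an under-count hurts it. Only this step's exposure is confined to the control side.
- **A reader might infer that 54 extra events would make the test significant with no programming effect.** They bring only the expected z to 1.96, which is about an even chance of significance. Nothing shows that the unlabelled subset of one source trial holds 54 shocked episodes, still less 54 net errors in one direction.
- **Classifying is better than dropping.** Agreed. The article gives that reason, and no bad faith is suggested.

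**Conclusion.** The concern holds in limited form. MIRACLE ICD episodes without adjudication receive their first classification from a scientist of the device manufacturer, in a batch drawn only from a control-source trial, with no masking to trial stated. That exposes the control count, and so the primary comparison, to classification bias of unknown direction and size.

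The figures above are sensitivity ranges, not estimates. They assume 503 years per arm, Poisson counts, 351 as the correct control count, and net errors that are a stated share of that count. The 99% share uses the narrower count in Statistical analysis, because no control figure for inappropriate shocks is given. The article also does not say whether the 347 already includes provisional labels for the episodes still to be reviewed.

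The ranges show that a modest net error, 5% to 10% of control events, would matter. They do not show that such an error is likely. The point merits a change of procedure, but does not by itself invalidate the comparison.

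**What to change.** 1. Have the existing reviewer, or the existing committee, classify these episodes in a set mixed with a sample of PREPARE and EMPIRIC episodes. Remove trial and calendar date, but keep timing relative to procedures, which may be needed to judge whether an episode was induced.
2. Lock the labels before any PREPARE event rate is tabulated.
3. State how many MIRACLE ICD episodes were newly classified. Report the primary result with the newly classified or indeterminate episodes counted all as induced, then all as spontaneous.

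The cost is some data preparation and extra reading. If the committee does the work, its stated remit has to widen. Masking will be imperfect, because the fixed PREPARE detection and therapy settings (Programming, Table 2) may be recognisable on the recordings. The bounding analysis costs almost nothing and would by itself show whether the classification could change the conclusion.
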